### Outcome Measures

The primary focus of this pilot is feasibility. Feasibility outcomes that will be reported include recruitment and enrollment rates, consent rate, retention and follow-up rates, adherence to the intervention (eg, time spent in scenarios and number of scenarios completed), data completeness, and adverse events or dropouts related to tolerability. Acceptability and usability outcomes will be assessed through participant responses and standardized instruments. Caregiver outcomes are collected as exploratory measures to describe change over time and to estimate variability for future studies. These caregiver outcome measures, completed at the 3 time points where indicated (Table 1), include:

Caregiver competence: Caregiver Competence Scale [26], a 4-item scale assessing perceptions of ability to manage caregiving tasks effectively.Resilience: Connor-Davidson Resilience Scale [27], a 10-item self-report questionnaire assessing ability to cope with adversity.Empathy: Empathy Assessment Scale [28], a 13-item scale evaluating cognitive and affective components relevant to caregiving.Stress: Perceived Stress Scale [29], a 10-item scale measuring perceived stress.Secondary exploratory measures include behavioral disturbances in people living with dementia (Neuropsychiatric Inventory) [30], depressive symptoms (Center for Epidemiologic Studies Depression Scale) [31], caregiver burden (the Burden Questionnaire) [32], and quality of life (Adult Carer Quality of Life Questionnaire) [33].

VR-SIM Carers is also being evaluated for its feasibility, acceptability, and tolerability on caregiver outcomes, and these will be assessed at multiple points. For technical feasibility, participants will be asked about their ability to carry out the study workflow and the amount of time they engaged with the VR scenarios. Recruitment and retention will be tracked to inform feasibility. For acceptability, participants will be asked about willingness to use the MVP on the expression of interest form and consent form. For tolerability, participants will be asked about any side effects related to hardware or software at the week 1 phone check-in, and the number of dropouts due to adverse events will be tracked.

Participants will also complete evidence-based scales that inform acceptability and tolerability. The 18-item Gaming Use Engagement and Severity Scale [34] assesses user satisfaction, usability, and system quality, while the Igroup Presence Questionnaire [35] measures spatial presence, involvement, and realism in VR environments. The Simulator Sickness Questionnaire documents the type and severity of side effects due to hardware and/or software use.

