### Participants

Participants will be recruited from various partner sites and complete an expression of interest form to self-refer to the study. Partner sites are responsible for sharing our research ethics board (REB)-approved recruitment material for this study. To be eligible to participate, the following inclusion criteria should be met:

18 years of age or older.Able to provide informed consent.Current unpaid family caregivers or care partners of people living with dementia.Caring for an individual with either suspected or diagnosed dementia. A formal diagnosis is not required.No self-report of active or unstable major psychiatric conditions (eg, major depressive disorders, bipolar disorder, schizophrenia). The study co-principal investigator or joint senior author and geriatric psychiatrist AMB will make the final decisions if necessary.Able to read and speak English and able to (1) participate in prototype testing, (2) participate in a postintervention feedback survey, and (3) follow instructions from research staff and complete self-administered surveys or assessment tools.

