**Weeks 2 and 3: Self-paced learning on VR-SIM Carers**
Self-completion of VR simulation scenariosReview virtual clinician’s feedback; program resourcesComplete check-in phone call from the study team

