### Progression Criteria

We prespecified quantitative and qualitative progression criteria to guide decisions about whether to proceed to a future definitive trial. Key thresholds are recruitment success 80% or higher (≥24/30 participants) of the target, amend-and-reassess if 50% to 79% (15-23/30) are enrolled, and stop or redesign if less than 50% (<15 participants) are enrolled. Retention success is 80% or higher completion of both postintervention and 1-month follow-up assessments, amend if 60% to 79% (18-23/30) complete, and stop if less than 60% (<18 participants). Intervention adherence success is 75% or more of the participants (≥23/30 participants) completing at least 2 of 3 scenarios and reviewing virtual clinician feedback during the loan period, amend if 50% to 74% (15-22/30), and stop if less than 50% (<15 participants). Data completeness success is 90% or higher (≥27/30) at baseline and 80% or higher (≥24/30) at post-intervention and 1-month follow-up for primary caregiver measures; amend for baseline 75% to 89% (≥23/30) or post-intervention or 1-month 60% to 79% (18-23/30). Safety or tolerability success is 15% or lower (<4 participants) reporting moderate or severe simulator sickness or adverse events attributable to device or software and no serious adverse events, amend if 16% to ‐30% (5-9/30) report moderate symptoms that are remediable, or stop if more than 30% (>9 out of 30 participants) report moderate or severe symptoms or any serious adverse event attributable to the intervention. Acceptability success is 70% or higher (≥21/30 participants) reporting willingness to use the MVP again or recommend it, amend if 50% to 69% (15-21/30), or stop if less than 50% (<15/30). Qualitative signals from interviews, reflection notes, and field notes will be used alongside these thresholds to interpret feasibility. Decision rules are to proceed to a definitive trial without substantive changes if most key criteria meet success thresholds, proceed with specified protocol modifications if criteria fall in the amend range but no major safety signals exist, and stop and redesign if multiple key criteria fall in the stop range or qualitative data reveal fundamental, unresolvable concerns. All progression decisions will be reported and justified in the Results section, and the CONSORT pilot flow diagram will present numbers screened, enrolled, completed at each time point, and the reasons for nonparticipation or dropout.

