### Ethical Considerations

This study has received ethical approval from the Ontario Shores Centre for Mental Health Sciences Joint Research Ethics Board (JREB 22‐031-B) and secondary approval from the NRC Research Ethics Board (NRC-REB 2023‐23). All participants will provide written informed consent at the time of the in-person orientation session, prior to taking part in any study-related activities. Participation is voluntary and compensated as approved by the research ethics boards, and all data will be deidentified and stored securely in accordance with institutional data protection guidelines. Any identifying information will be kept separate from research data and accessible only to trained research personnel. Participants will be informed of their right to withdraw from the study at any time without consequence. Study findings will be broadly disseminated through peer-reviewed publications, conference presentations, and reports to stakeholders and funders. Knowledge users’ feedback gathered throughout the pilot study will inform future iterations of the VR-SIM Carers MVP and implementation. In addition, a publicly accessible project website will feature blog posts and community updates to extend our outreach effort. By sharing our findings with both academic and community audiences, we aim to contribute to capacity building, as well as establishing the evidence base for scalable, technology-enabled psychoeducation tools for family caregivers or care partners of people living with dementia.

As aforementioned, local ethics clearance has also been received from each recruitment site’s research ethics board.

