### Limitations

Several limitations should be acknowledged. The small sample size, although appropriate for a pilot study, limits the statistical power to detect moderate effects and reduces generalizability. For this initial pilot, only English-speaking participants are included, and participants will not be experiencing significant psychological distress, which may exclude some caregivers most in need of support. The pilot’s self-referral recruitment process through the expression of interest form may introduce selection bias, favoring individuals more open to using novel technology. Additionally, variability in participants’ familiarity with VR technology could affect the consistency of the intervention’s delivery. The in-person orientation session, although centrally located, may be a barrier to participation. Finally, individuals in the early stages of dementia typically do not exhibit the behavioral and psychological symptoms of dementia that the VR-SIM Carers MVP is designed to address; as such, the intervention may have limited relevance for caregivers supporting individuals in these early stages [43,44]. These limitations will be carefully considered in interpreting pilot findings and designing future larger-scale studies in diverse caregiver populations (eg, cultural groups) and settings (eg, community vs long-term care).

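### The only willingness item named for acceptability is asked before the headset is used, but the progression criterion needs an answer that exists only after use, and no post-use source is linked to it

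*Protocol article*

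**What the plan says.** Three parts of the Protocol article bear on this.

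- **Measurement (Outcome Measures).** The sentence that operationalises acceptability is "For acceptability, participants will be asked about willingness to use the MVP on the expression of interest form and consent form". The same section says in general terms that acceptability will be assessed through participant responses and standardised instruments, and adds: "Participants will also complete evidence-based scales that inform acceptability and tolerability". Table 1 schedules the user-experience scale, the presence scale and four open questions at 1 month. Textbox 1 adds a week 4 interview and the handing in of reflection notes.
- **Decision rule (Progression Criteria).** "Acceptability success is 70% or higher (≥21/30 participants) reporting willingness to use the MVP again or recommend it"; the lower bands are "amend if 50% to 69% (15-21/30), or stop if less than 50% (<15/30").
- **Timing.** Under Participants, candidates "complete an expression of interest form to self-refer to the study". Under Ethical Considerations, "All participants will provide written informed consent at the time of the in-person orientation session, prior to taking part in any study-related activities". Textbox 1 places headset orientation after consent in week 1, and scenario use in the block headed "Weeks 2 and 3: Self-paced learning on VR-SIM Carers".

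**The concern.** The item and the criterion are different quantities at different times. The item records whether someone who has not yet used the product is willing to try it. The criterion asks whether someone who has used it would do so again or would recommend it. Everyone in the enrolled denominator has put themselves forward for a VR study and agreed to take a headset home, so a pre-use answer can hardly vary. The Limitations section itself says that self-referral "may introduce selection bias, favoring individuals more open to using novel technology".

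Acceptability belongs to the primary objective and is one of six progression criteria (recruitment, retention, adherence, data completeness, safety or tolerability, acceptability). The rule is to proceed when most of them succeed. A criterion scored from the pre-use item would count toward proceeding whatever users thought afterwards. If the pre-use item is not meant to be scored, the article leaves open what is.

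**Working it through.** **Inputs from the article.** Planned sample 30 (Sample Size). Success at 70% or more, given as at least 21/30; amend at 50% to 69%, given as 15-21/30; stop below 15/30 (Progression Criteria).

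**Assumed inputs.** The article gives no expected willingness, before or after use. I take 95% or more before use, and a range of 50% to 90% after use. All 30 are taken to answer.

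**Step 1: the plan's own threshold.** 0.70 × 30 = 21, so the success figure reproduces. For the amend band, 0.50 × 30 = 15 and 0.69 × 30 = 20.7, so the whole-number band is 15-20. The printed upper limit of 21 is exactly 70% and also lies in the success band.

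**Step 2: order of events.**

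| Event | When |
|---|---|
| Expression of interest form (willingness asked) | Self-referral, before enrolment |
| Consent form (willingness asked) | Week 1, before any study activity |
| Headset orientation | Week 1, after consent |
| Scenario use | Weeks 2 and 3 |
| Interview, headset return, reflection notes | Week 4 |
| Two scales, four open questions | 1 month after |

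Both placements of the named item precede use. Every planned post-use source is described without a use-again or recommend question and without a rule for turning it into a count.

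**Step 3: chance of meeting the success rule.** With X ~ Binomial(30, p), P(X ≥ 21) is the sum over k = 21 to 30 of C(30, k) p^k (1 − p)^(30 − k).

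| Assumed true proportion p | P(X ≥ 21) |
|---|---|
| 0.50 | 0.021 |
| 0.60 | 0.176 |
| 0.65 | 0.358 |
| 0.69 | 0.541 |
| 0.70 | 0.589 |
| 0.80 | 0.939 |
| 0.90 | 0.9995 |
| 0.95 (pre-use item) | above 0.9999 |

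A post-use item separates the bands, if roughly at this sample size. A pre-use item at 95% or more does not separate them at all.

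**Step 4: effect of missing answers.** If only 24 of 30 answer and 21 positive answers are still required, P(X ≥ 21) with X ~ Binomial(24, 0.80) is 0.264, against 0.939 with all 30. The denominator and the handling of non-response therefore have to be fixed in advance.

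**The case against.** The strongest reply is that the article never says the pre-use answers will be scored against 21/30. The word for repeat use in the criterion calls for a post-use response on its own terms, so the near-certain pass is conditional on a substitution that is not stated. This stands, and the probabilities above should be read as what would happen if the only named willingness item were used.

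Second, post-use acceptability data are planned, and a reader might infer from the quoted sentence that the plan yields no information on acceptability. The text does not support that. The scales, open questions, interviews, reflection notes and check-in notes all bear on it, and the decision rule lets qualitative findings lead to a redesign. However, the scales are described as covering satisfaction, usability, system quality and presence, not reuse or recommendation. Interviews are to be analysed by inductive thematic coding, which does not of itself give a count. Qualitative signals are used next to the thresholds, not as their numerator.

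Third, Table 1 lists instruments, not items. The interview guide is in an appendix that is not shown, and the wording of the four open questions is not given, so a suitable item may exist. This stands too: what is shown is a missing link, not a proven missing measurement.

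Finally, a reader might infer that asking about willingness on the expression of interest form means collecting outcome data before consent. That would require treating self-referral as a study-related activity, which the article does not do, so the inference is not supported.

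**Conclusion.** The point holds as a conflict between two stated sections. Outcome Measures names one willingness item, placed before use; Progression Criteria grades a response that can exist only after use; nothing in the article connects the planned post-use data to the count out of 30.

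Scoring the named item would turn a 2% to 54% chance of success across the amend range into near certainty. That comparison rests on three assumptions: pre-use willingness of at least 95%, which is inferred from self-referral and consent and is not a figure in the article; independent responses; and all 30 answering. The conflict between the sections needs none of these assumptions. The overlap at 21/30 is a separate arithmetic slip in the same criterion and is certain.

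**What to change.** 1. In Outcome Measures and Table 1, name two closed items, would use again and would recommend, self-completed at headset return: the week 4 visit, or the earlier return date for anyone who stops early. If the unseen interview guide or the 1-month questions already contain such an item, name it and link it to the criterion instead.
2. State the response cut-off that counts as willing. Count a participant as a success if either item is endorsed, since the criterion joins the two with an or.
3. Use all enrolled participants as the denominator, with non-responders counted as not willing, and report a respondents-only proportion alongside.
4. Report the expression of interest and consent answers only as a description of who came forward, outside the criterion.
5. Correct the amend band to 15-20/30.
6. Ask participants already past week 4 in the 1-month survey where that is still open, and flag their answers as collected at a different time.

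The cost is two survey items at an existing visit, one row in Table 1, a few sentences of text and probably a minor ethics amendment. It is pressing: the article reports 21 participants enrolled by December 2025 and data collection ending in March 2026, so each further week 4 visit without the items loses an answer at the intended time.

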### Data Analysis

#### Qualitative Data

An inductive thematic analysis will be conducted on qualitative data collected from the week 4 audio-recorded interviews with study participants. Interviews will take 30 to 45 minutes and will be facilitated by SCP, KMC, and EO following a semistructured interview guide (Supplementary file B in Multimedia Appendix 1). Secondary sources of qualitative data will include participant reflection notes, the week 2 or 3 check-in phone call, and the 1-month qualitative written feedback survey questions. This multimodal approach is intended to capture participants’ experiences and perspectives over time. The audio recordings of the semistructured interviews will be transcribed verbatim by research staff and will serve as the primary qualitative data source. Transcripts, reflection notes, and field notes will be imported to Dedoose (9.0.107) for analysis [36].

To create the codebook in Dedoose, 3 (MC, SCP, and KMC) members of the study team trained in coding will independently review 3 interview transcripts to generate an initial set of codes and to collaboratively develop a codebook through consensus [23]. To reduce potential bias, the member who transcribed an audio-recorded interview will not be assigned to code that same transcript. A tracking sheet will be created to manage coding assignments and ensure consistent review.

#### Quantitative data

Descriptive statistics will summarize participants’ demographic characteristics and feasibility metrics. Statistical analysis will be completed using SPSS (version 29; IBM Corp) [37]. Paired 2-tailed *t* tests may be used to assess within-subject changes between specific time points as exploratory analyses. Repeated measures statistics will be used to describe change across the 3 time points. Consistent with CONSORT guidance for pilot and feasibility studies, caregiver outcomes (eg, competence, stress, resilience, empathy) are treated as exploratory, and no causal claims regarding intervention effectiveness will be made. Observed changes over time may reflect nonspecific effects such as time, expectancy, repeated measurement, or general study contact (eg, orientation and check-in calls). Repeated measures are collected to describe the direction and magnitude of change over time and assess the feasibility and sensitivity of the selected measures in this population and delivery format. All quantitative analyses are intended to estimate variability and inform sample size calculations and protocol decisions for a future definitive trial. A 2-sided *P* value of <.05 may be reported for descriptive purposes, but hypothesis testing is not the primary aim of this pilot.

### Study Monitoring

Upon enrollment, each participant will be assigned a unique study number. Any research-related information collected (eg, surveys, scales, and questionnaires) will be labeled and stored using this study number to deidentify personal information and uphold confidentiality. A master list linking participant names to their unique study number will be stored separately on the Ontario Shores secured network, which will be password-protected and accessible only to authorized study personnel. Written documents (eg, consent forms) will be stored in a locked filing cabinet at the Ontario Shores Research and Academics Office, with access restricted to study-approved staff.

Survey and deidentified interview data will be password-protected and accessible only to authorized study personnel. Audio recording files will be deleted once transcribed, and identifying information will be removed. Check-in call field notes will be deidentified as well. All study data will be stored on the Ontario Shores Secured Network Drive and will be aggregated for reporting. All assessment tools and scales will be provided on SimpleSurvey [38], a secure survey platform that will allow each participant easy access to completing surveys at their own pace. The data will remain in SimpleSurvey for 60 days following termination of the account in November 2025 [39]. The data collected through this research study will be stored securely for a 7-year period and will be monitored and reviewed by study investigators to ensure confidentiality protocols are upheld, following REB guidelines and protocol procedures.

### Patient and Public Involvement

As per the guidelines of the VR-CORE framework (VR1 phase), the MVP was shaped through a collaborative and iterative process involving demonstration outreach and knowledge summit activities [40,41]. Initial exposure of the pre-MVP prototype to attendees from these events provided the opportunity for diverse backgrounds (clinicians, researchers, and potential end users) to provide feedback on their interaction. Although this feedback did not contribute to the overall study design, attendees’ feedback provided input regarding usability, technological requirements, clinical relevance, and practical considerations that informed the iterative development of the MVP.

As part of these outreach efforts, a detailed manual was presented to all participants at the knowledge summit to guide them through the MVP’s features and activities and support more structured reflection and feedback. This helped to ensure users had a basic understanding of the prototype’s intended functions and use. Additionally, this project benefited from an advisory board that included knowledge users ([name] and [name]), who provided further review and guidance.

To assess the feasibility of the MVP developed, protocol, and user experience, 3 clinician externs from Ontario Shores Centre for Mental Health Sciences engaged in a mock structured run-through of the protocol. First, an orientation session was conducted; then, externs took the VR headset home for 1 week to experiment with the scenarios and review the manual. Their involvement allowed for the real-time identification of the duration of our set activities and addressed any accessibility or technological concerns about the MVP and orientation flow. Feedback led to improvements in system navigation, onboarding materials, and improved preparedness of the study team for subsequent caregiver cohort orientation sessions.

